#### Patient and public involvement statement

During the entire experimental period, conversations will be held with the subjects about their experiences, with the aim of understanding and improving their experiences in current and future premeal intervention trials.

## Discussion

This is the first trial that directly assess the effects of three types of natural snacks on GV. One of the primary aims of this study is to determine which type of snacks is better for GV improvement. Short-term and long-term studies showed that high-protein and high-fat snack interventions could improve glucose metabolism, β cell function, lipid profile, satiety, and body weight, etc. (34–38), while previous experiments also reported that high-protein snacks were better at reducing hunger, bringing satiety, and reducing energy intake for the next meal (39). We hypothesize that all three types of snacks could improve GV and perhaps high-protein snacks have a better effect. In addition, most previous studies focused on separate animal-based protein and suggested that premeal animal protein has a superior effect on glycemic control, probably because of the high branched-chain amino acid content of whey protein, which allows for faster digestion and absorption of milk, causing a significant postprandial amino acid response and rapid first-phase insulin release (40, 41). However, none of these studies assessed the effect of plant-based and animal-based high-protein natural snacks on GV. In this trial, we will directly compare the effects of these two types of high-protein snacks and expect to observe a non-inferiority effect of soy powder compared to milk powder. We also hypothesize a non-inferiority effect of plant-based high-protein snacks (whole soy powder) compared with animal-based high-protein snacks (milk powder) on GV improvement. If this hypothesis is proven, the effective use of soy powder could also provide more options for the lactose-intolerant population.

Another important advantage of the trial is that we will implement a premeal snack intervention under two different dietary conditions. Several studies have reported the beneficial effects of premeal snack interventions on glucose metabolism under well-controlled dietary patterns (14, 40, 42). Although the effects observed in this way are significant, such studies under well-controlled conditions could not represent the full extent of this benefit in real daily diet because GV itself can vary with the order of meals, macronutrient ratios, and the interval between meals (11). The purpose of this design is to determine whether the intervention, when applied to a daily diet, will result in improvements similar to those obtained under the experimental control diet. First, before the start of the experiment, we will set a run-in period with the aim of testing the baseline GV levels of the subjects as their own control. After the run-in period, the first period of the intervention will begin, and premeal snacks will be given under exactly the same habitual diet conditions as those in the run-in period, during which no restrictions will be imposed on the amount and type of food consumed by the subjects at their regular meals. After the end of the first intervention period, a standard balanced meal run-in period will be set to ensure that the subjects' metabolism adapts to this meal pattern before the start of the second intervention period, to obtain more stable data for the second-period results.

Notably, as the prediabetic population continues to expand, the solution to reduce the risk of the development of diabetes in this population is an urgent issue. It has been reported that in the process of disorders in glucose metabolism, the increase in postprandial glucose excursion and delayed duration of postprandial glucose excursion occurs earlier than the increase in FBG levels in patients with prediabetes (43). Our study will select subjects from the pre-diabetic population aim to alleviate glucose metabolism and achieve prevention through simple and easily implemented lifestyle interventions. In addition, the results from the prediabetic population are more likely to be extrapolated to diabetic populations.

Furthermore, we will control for confounding factors as strictly as possible. This protocol is based on past studies of the effects of different intervention time points, intervention foods, intervention energies, and intervention populations. However, this study is extended by physical activity level monitoring and daily nutritional recordings (electronic food diary, CGM, and activity records) through timely supervision of the subjects by the researchers and hunger, satiety, and blood glucose and insulin resistance indices will be measured before and after energy intake. During both the ad libitum and standard meal periods, subjects will be asked to record whether and how much food is left over from each meal to assess the effect of the intervention on energy intake at regular meals and to exclude changes in GV due to differences in energy intake. To exclude the influences of different dietary patterns, researchers will train the subjects to eat in the same fixed meal order and have the same duration of each meal (chewing pace) to control for confounding factors in the 3-day balanced meal run-in period. At the end of the experiment, subjects will also be surveyed about their perceptions of the intervention to obtain information about its acceptability, compliance, and adherence. Compared to previous studies, these tools and measures will help avoid confounding factors, advance the understanding of the effect of the premeal snacking intervention on GV and promote the application of the intervention to a wide range of the population. Moreover, we will also administer 250 ml of water to the control group, similar to the 3 intervention groups, to avoid the influences of stomach capacity and swallowing behavior changes on the results (44, 45). In addition, for data processing, we will exclude data from the first day of each phase and the last day of wearing the CGM to exclude data differences caused by the instability of CGM devices.

In conclusion, this is the first RCT protocol that directly compares the effects of different natural snacks under different dietary patterns on GV. We will carry out a careful and rigorous research protocol for the following three issues we want to study: [1] the comparison of GV improvement effects between high-protein snacks and high-fat snacks; [2] the comparison of GV improvement effects between animal-based high-protein snacks and plant-based high-protein snacks; and [3] the comparison of the effects under two different dietary patterns. The limitation of this study is that we will use nuts eaten with water instead of nut powder solution. Because the high-fat powder solution does not have good compliance, we will consider the acceptability of the subjects. Therefore, there may be confounding factors caused by chewing activities in the whole nut group. In addition, the number of people included in this study will be quite small, so the conclusions should be extrapolated with more people. Another limitation of this study is the short duration of the experiment, with only 4 days per period. This is because the maximum validity of a single CGM device is only 14 days. Therefore, the effects we derive will represent only acute effects, and more long-term anthropometric and metabolic outcomes will need to be validated with longer-term experiments.

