In studies of the second meal effect, the meal pattern is also very important to the results. Most of the currently proposed premeal intervention studies are conducted under well-controlled laboratory conditions with uniformly balanced diets or use glucose tolerance tests to simulate eating behavior. Although the effects were obvious, it is not clear that similar benefits can be achieved under real daily diet conditions. Moreover, single nutrients or intervention foods in experimentally specific ratios are not readily available in daily life and are difficult to adapt to the different dietary habits of people in China and other regions, which may lead to poor adherence. Therefore, we will select easily accessible natural foods, i.e., soy powder, milk powder, and almonds, to represent high plant protein, high animal protein, and high fat premeal snacks intervention, respectively, and evaluated their effects on GV under two different dietary patterns: habitual diets and balanced standard meals. In this trial, we will fully consider dietary habits, offer common foods as premeal snacks without energy restrictions, and detect the effects on GV and energy intake. Our trial is expected to have high applicability, operability, and acceptability, which can provide evidence for further application in T2DM populations.

The primary aim of this study is to evaluate whether premeal snacks of natural foods improve GV and which kind of premeal snacks lead to better effects in prediabetic subjects. We hypothesize that plant-based high-protein snacks will lead to a non-inferiority effect of animal-based high-protein snacks on GV. The secondary objective is to evaluate whether these interventions have a positive effect on insulin, HOMA-IR (homeostasis model assessment for insulin resistance), HOMA-β (homeostasis model assessment for β cell function), C-peptide, body weight, waist circumference, abdominal circumference, subjective appetite, hunger, and satiety. Furthermore, we will assess the acceptability and maintainability of these interventions.

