**Withdrawal criteria**
• Participant's withdrawal of informed consent • Noncompliance with consuming the study foods

*FBG, fasting blood glucose; IFG, impaired fasting glucose; PG, postprandial glucose; IGT, impaired glucose tolerance*.

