### Standard balanced meals run-in period

A 3day run-in period will be scheduled between Visit 2 (V2) and Visit 3 (V3), during which subjects will be asked to maintain the same levels of rest and physical activity as they did during the experimental period. Subjects will be given standard balanced meals 3 times per day during the run-in period and will not be provided with premeal snacks. Furthermore, researchers will train the subjects to eat in the same fixed meal order and have a similar duration of each meal (to keep a similar chewing pace) to control for confounding factors.

Standard balanced nutrients will be given for each meal during the second intervention period. Calories will be matched between groups for each meal and a total 24-h period within participants. Energy requirements for the day will be divided by sex calculated with the participants' average using the Harris-Benedict formula (29).

Males: resting metabolic rate (kcal/d) = 66.5 + (13.75 × weight in kilograms) + (5.003 × height in centimeters) − (6.775 × age in years);

Females: resting metabolic rate (kcal/d) = 665.1 + (9.563 × weight) + (1.850 × height) − (4.676 × age).

The energy allocation will be 30, 40, and 30% for breakfast, lunch, and dinner, respectively, with macronutrient ratios following the dietary guideline recommendations of 50–55% of calories from carbohydrates, 15–20% from protein, and 25–30% from fat. Daily meals will include vegetables, meat, and staple foods. After this trial, we will upload the realistic standard meals in the form of a photograph. The types of food are shown in Table 4.

**Table 4 T4:** Food types of standard meals.

**Food type**	**Staple food**	**Vegetable**	**Protein**
Breakfast	Noodles	Tomato	Egg
	Bread	Cucumber	Milk
	Rice	Cabbage	Pork
Lunch and dinner	Rice	Broccoli	Fish
		Cabbage	Chicken
		Carrot	Pork
		Mushroom	Egg
		Tomato	

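### Energy intake after the snack is a result of the snack, yet the Discussion proposes to exclude its influence from the glycemic variability effect; the main comparison should be stated as unadjusted for it

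*Protocol article*

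**What the plan says.** All references are to the protocol article.

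- **Discussion, paragraph on confounding.** It opens: "Furthermore, we will control for confounding factors as strictly as possible". It then says, of every meal: "During both the ad libitum and standard meal periods, subjects will be asked to record whether and how much food is left over from each". Two purposes are given for that record: "to assess the effect of the intervention on energy intake at regular meals and to exclude changes in GV due to differences in energy intake".
- **Introduction.** The trial will "offer common foods as premeal snacks without energy restrictions, and detect the effects on GV and energy intake". The primary aim is whether premeal snacks of natural foods improve GV and which kind does so best.
- **Discussion, first paragraph.** Earlier experiments are cited as showing that "high-protein snacks were better at reducing hunger, bringing satiety, and reducing energy intake for the next meal".
- **Discussion, on the habitual-diet period.** In the first intervention period "no restrictions will be imposed on the amount and type of food consumed by the subjects at their regular meals".
- **Standard balanced meals run-in period.** For the supplied meals, "Calories will be matched between groups for each meal and a total 24-h period within participants".
- **Statistical analysis plan section.** It lists paired t-tests, ANOVA, Dunnett's test and non-parametric alternatives. It names no energy-intake covariate and no removal of days or participants because of leftovers.

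**The concern.** One sentence gives the same record two roles. In the first half, intake at meals is something the snack changes and the trial measures. In the second half, it is a disturbance to be taken out of the GV result. Both cannot hold for the main comparison.

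A confounder in a randomised trial would have to be a chance imbalance present before treatment. Intake after the snack arises after treatment and, on the article's own reasoning, partly because of it. It is a candidate mediator. Removing its influence changes the question from whether the snack improves GV to whether it would do so if it did not alter eating. It also breaks the protection of randomisation, because people who eat less after a snack may differ in other ways that affect glucose.

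The comparison between diet patterns is at stake too. The Comparisons section ends by asking whether the snacks act alike under habitual and standard meals. Freedom to eat less is a main difference between those two conditions, so stripping out intake would blur that contrast.

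**Working it through.** **1. Is post-snack intake a consequence of allocation?** Yes, on the document's own terms. The Introduction lists energy intake as an effect to be detected, and the Discussion says high-protein snacks lower intake at the next meal. In period 1 intake is free to respond. In period 2 the calories supplied are matched, so intake can differ only through leftovers or extra food. The record covers every meal, not only lunch.

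**2. How could the clause be carried out?** Leftovers are recorded after eating, so the record cannot prevent intake differences. It can remove their influence only in the analysis, by adjustment or by dropping days or people.

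**3. Is such a step in the listed methods?** No. As listed, ANOVA and Dunnett's test on changes keep the total effect.

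**4. What would happen if it were applied?** The documents give no mediated share, so this is an illustration on **assumed** inputs only. Let T = 1 for snack and 0 for control, U an unmeasured common cause, and all random terms independent with SD 1:

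- Intake: M = -T + uU + e1
- GV: Y = -(1 - s)T + sM + uU + e2

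Here s is the share of the effect that runs through intake. Total effect = -(1 - s) - s = -1 for every s.

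*Adjusting for M.* The coefficient on T is -(1 - s) + u²/(u² + 1). With u = 0 the second term is 0. With u = 0.5 it is 0.25/1.25 = 0.20.

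*Dropping low intake* (below the control arm's 25th percentile, -0.674; u = 0). Mean intake among those kept is 0.424 in control and 0.016 in the snack arm, a difference of -0.408. The estimate is -(1 - s) - 0.408s.

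| Share s | Unadjusted | Adjusted, u = 0 | Adjusted, u = 0.5 | Low intake dropped |
|---|---|---|---|---|
| 0 | -1.00 | -1.00 | -0.80 | -1.00 |
| 0.25 | -1.00 | -0.75 | -0.55 | -0.85 |
| 0.50 | -1.00 | -0.50 | -0.30 | -0.70 |
| 0.75 | -1.00 | -0.25 | -0.05 | -0.56 |

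A simulation with 400,000 participants per scenario agrees to within about 0.01. Dropping low intake keeps about 37% of the snack arm against 75% of control. With a common cause, adjustment is biased even when nothing runs through intake. The bias is towards zero here because U was assumed to move intake and GV in the same direction; opposite directions would reverse it.

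**5. Room for loss.** The Sample size determination section needs 6 per group and allows 20% dropout: 6/0.80 = 7.5, rounded up to 8, or 32 over four arms. That figure reproduces and is not in dispute. It shows that losing more than two participants in an arm would leave fewer than the planned 6.

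**The case against.** The strongest reply is that no exclusion rule exists. The clause states a purpose in the Discussion, and the same paragraph uses the verb loosely: the influence of dietary pattern is to be excluded by training meal order and pace, which removes no data. Where data are to be dropped, as for certain glucose-monitor days, the article says so outright. Read this way, the clause means only ruling out lower intake as the explanation for a GV change, which is a fair mechanistic aim alongside measuring intake. Much of this stands, and it is why the harm is conditional. What it does not remove is a stated intention, framed as confounder control, that conflicts with the primary aim and could be acted on only in the analysis.

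Three stronger readings are tempting but not supported:

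- **The plan as written removes part of the effect.** A reader might infer this, but the listed tests include no adjustment or restriction.
- **Leaving part of a supplied meal is a ground for withdrawal.** Table 1 lists "Noncompliance with consuming the study foods", and a reader might take that to cover the standard meals. The term is undefined, may mean only the snacks, and is not tied to leftovers anywhere. It is a point to clarify, not an error.
- **The lost share can be set against the expected 20% fall in MAGE.** A percentage cut in one lunch excursion is not comparable with a percentage cut in MAGE, which averages over excursions. The documents give no leftover fraction, and the snack itself adds 83 to 90 kcal and 2.7 to 14.0 g of carbohydrate (Table 3).

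**Conclusion.** The point holds as a conditional one. The Discussion states an intention to take intake-driven change out of the GV result, while the Introduction and Discussion treat intake as an effect of the snack and the primary aim asks for the total effect. If the intention is applied, any intake-mediated part of the effect is removed and bias may be added, above all under the unrestricted habitual diet. If it is not applied, the listed comparison keeps the total effect.

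The size is unknown. The illustrated losses rest on an assumed one-SD fall in intake, assumed mediated shares and an assumed common cause, and say nothing about the true figures. The conclusion rests on only two premises: intake after the snack can respond to it, as the article says, and the primary aim is the total effect on GV.

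**What to change.** 1. In the Discussion, delete the clause on excluding GV changes due to energy intake, or reword it to say that the record helps interpret how any GV effect arises.
2. In the statistical section, state that the main GV comparison in each period is neither adjusted for nor restricted by post-snack energy intake or leftovers.
3. Present any intake-adjusted result as a labelled exploratory mechanistic analysis, noting that it may be confounded by common causes of intake and GV.
4. Clarify in Table 1 what the term study foods covers, and reconcile it with the leftover record, so that the two passages cannot be read against each other.

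The cost is a few lines of text. The only statistical downside is somewhat more intake-related variation in the main comparison. The leftover record and the trial procedures stay as they are.

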## Ethics and dissemination

The study was approved by the Medical Ethics Committee of The 2nd Affiliated Hospital and Yuying Children's Hospital of WMU and will be conducted following the Declaration of Helsinki. All equipment used in the study will meet the requirements for subject safety. The total amount of blood taken at each visit will be a maximum of 5 ml and is considered to be safe. The data and biorepository have been approved by the Chinese Data Protection Authority. All research-related information will be recorded, processed, and stored securely in a manner that allows accurate reporting, interpretation, and validation. For CGM measurements, source data will be registered in the web-based software using the subject's study ID. The sponsor/investigator will have direct access to the source data/files for regulatory checks. Anyone can send a request email to the principal investigator to access the full experimental data. Information on injuries/side effects will not be systematically recorded, as we do not expect to cause harm associated with the intervention. All of the positive, negative, or inconclusive findings will be presented at a conference and published in international peer-reviewed journals following the CONSORT guidelines, with no publication restrictions imposed (46).

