## Methods and analysis

### Study design

This study is a single-center, open-label, multiparallel group, randomized controlled trial. The study consists of two intervention periods: [1] under habitual diet conditions and [2] under balanced standard meal conditions. After a 3-day experiment run-in period, a total of 32 subjects (16 males and 16 females) will be randomized into one of 4 arms in 1:1:1:1 ratio (Figure 1). The 4 arms will include soy powder and milk powder which will be completely dissolved in 250 ml water, almond snacks with 250 ml of water, and a control arm (250 ml of water). Test days will be scheduled before and after the two intervention periods to assess the potential effects of premeal snacks under the habitual diet and standard balanced diet patterns, respectively. During the entire period of this experiment, subjects will be asked to complete a food recording diary (online) including the type, amount, and time of all meals, snacks, and drinks except water (in the form of photos and text). Physical activity and sleep will also be recorded via a mobile app for step count and sleep time records. The study will be performed at Wenzhou Medical University. The protocol followed the Standard Protocol Items: Recommendations for Interventional Trials statement (27).

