#### Secondary outcomes

Secondary outcomes consist of various metabolic and behavioral indicators, including changes in insulin, C-peptide, fasting blood glucose (FBG), HOMA-IR, HOMA-β, subjective appetite, satiety, hunger evaluated by the VAS, body height, and weight measurements.

We will assess changes in these outcomes in two different experimental periods: [1] from baseline to the end of the first intervention period (D3-D6) and [2] from the end of the run-in period to the end of the second intervention period (D10-D13). The acceptability and maintainability of the intervention will also be assessed after the completion of the interventions (D14).

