#### Interviews

Face-to-face interviews will be conducted at V4 to evaluate the participants' experiences and perceptions of the intervention in depth. All subjects will be invited to a personal semistructured interview of ~20 min to explore the feasibility and acceptability of the premeal snack intervention being included in their daily dietary habits. It will help to understand the feasibility of the intervention and the acceptability and sustainability of integrating this intervention into their daily lives. If subjects withdraw from this trial, they will be invited to record their reasons for withdrawing and their perceptions of the interventions by a face-to-face interview.

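### Side effects are deliberately not recorded systematically, so the trial cannot reliably report side effects or snack tolerance by arm

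*Protocol article*

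**What the plan says.** The decision is in Ethics and dissemination: "Information on injuries/side effects will not be systematically recorded, as we do not expect to cause harm associated with the intervention". A few sentences earlier the same section gives a general undertaking: "All research-related information will be recorded, processed, and stored securely in a manner that allows accurate reporting, interpretation, and validation".

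Side effects appear neither among the primary and secondary outcomes nor in the schedule of visits (Table 2). The nearest data are these:

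- **V4 questionnaire.** Table 2 lists one on acceptability and compliance. The Discussion also mentions an end-of-study survey of perceptions, acceptability, compliance and adherence, which may be the same instrument.
- **V4 interview.** "All subjects will be invited to a personal semistructured interview of ~20 min to explore the feasibility and acceptability of the premeal snack intervention".
- **Withdrawal interview.** For participants who leave, "they will be invited to record their reasons for withdrawing and their perceptions of the interventions by a face-to-face interview".

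The online food diary runs for the whole study, and a researcher checks daily that it has been uploaded (Study design; Intervention). It is described as covering the type, amount and time of meals, snacks and drinks, not symptoms.

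**The concern.** The expectation that nothing will go wrong is the only reason given for not looking. Participants are nevertheless exposed to something. The three snack arms take soy powder, milk powder or almonds on D3-D6 and D10-D13. All arms wear a sensor for two weeks, take four glucometer readings a day and have venous sampling at V1 to V4.

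The between-arm question is how well the snacks are tolerated, because the sensor and blood-sampling burden is common to all arms. Not consuming the study foods is a withdrawal criterion (Table 1). If digestive discomfort lay behind poor compliance in one arm, no record made at the time would show it. The report could then say little about tolerance of foods that the Discussion hopes to see taken up by a wide range of people.

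**Working it through.** The point is mainly one of reading, so the passages are set side by side first. The arithmetic shows only how much recording could deliver.

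**1. Is the rule reversed anywhere?** No. The outcome sections, Table 2, Interviews, the statistical analysis section and the Discussion contain no collection of side effects. The idea of tolerability is applied only to the standard meals in the second run-in (Intervention), not to the snacks. A longer protocol or a separate analysis plan may hold more detail, but an analysis plan cannot analyse data that the trial has decided not to collect.

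**2. What would the existing sources give?**

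| Source | Who | When | Described as asking about side effects? |
|---|---|---|---|
| Acceptability and compliance questionnaire | All at V4 | Once, at the end | No |
| Semistructured interview, about 20 min | All, by invitation | Once, at V4 | No |
| Withdrawal interview | Those who withdraw, by invitation | At withdrawal | Reasons and perceptions only |
| Online food diary | All | Daily | No |

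A side effect could surface in any of these, but only if the participant raised it. Participants know their snack (Randomization and allocation concealment), so readiness to raise it may differ by arm. There would be a denominator but no dependable numerator.

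**3. Group sizes.** Sample size determination gives 6 per group and 20% dropout. 6 / (1 - 0.20) = 7.5, rounded up to 8, and 4 x 8 = 32. This reproduces the stated total. The three snack arms together hold 3 x 8 = 24.

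**4. What could be concluded with complete recording and no events?** The exact one-sided 95% upper limit for zero events in n participants is 1 - 0.05^(1/n), counting each participant once and treating participants as independent.

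- One arm, n = 8: 1 - 0.05^(1/8) = 0.312
- One arm, 6 completers: 1 - 0.05^(1/6) = 0.393
- Three snack arms, n = 24: 1 - 0.05^(1/24) = 0.117

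**5. How does incomplete capture matter?** The chance of seeing at least one event in an arm of 8 is 1 - (1 - pc)^8, where p is the true proportion affected and c the fraction captured. The documents give neither, so both are assumptions.

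| Assumed p | c = 1 | c = 0.5 |
|---|---|---|
| 5% | 33.7% | 18.3% |
| 10% | 57.0% | 33.7% |
| 20% | 83.2% | 57.0% |

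If half of events go unmentioned, an arm in which 20% are affected shows none with probability 1 - 0.570 = 43%, against 1 - 0.832 = 17% with full capture. Since c would be unknown and could differ by arm, no bound of the kind in step 4 could be stated.

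**The case against.** The expectation of no harm has some support. The snacks are ordinary foods of 80-90 kcal; food allergy and gastrointestinal disease or discomfort are exclusion criteria; ethics approval is stated; and blood volume is capped at 5 ml per visit. With 8 per arm, even perfect recording could not show that a snack is well tolerated or that arms differ. All of this stands, and it limits the weight of the point. It does not make unsolicited reports a substitute for asking.

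Four stronger readings are tempting, and the documents do not support them.

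- **Nothing about side effects could be reported, or only one end-of-study interview would reveal them.** Not recording systematically does not bar incidental recording, and the V4 questionnaire and withdrawal interviews also exist. What is lost is reliable reporting by arm.
- **The Discussion makes a tolerability claim for soy.** The statement that "the effective use of soy powder could also provide more options for the lactose-intolerant population" depends on soy proving non-inferior to milk on glycemic variability. It is an inference from efficacy, not a promise of tolerance data.
- **The rule breaches the reporting standard.** Results are to be "published in international peer-reviewed journals following the CONSORT guidelines, with no publication restrictions imposed", but the documents do not say what that standard requires on harms. A report could disclose that side effects were not systematically collected.
- **Making acceptability an aim contradicts the rule.** Acceptability is described as fitting the snack into daily eating, which is a different quantity from side effects.

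The undertaking to record all research-related information can also be read as being about data handling. It sits uneasily beside the rule without strictly contradicting it, and the two sentences should be reconciled.

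**Conclusion.** The point holds, at the level of something that should be changed rather than something that undermines the trial. Followed as written, the trial would have only incomplete, retrospective and unsolicited information on side effects. It could not reliably report side effects or snack tolerance by arm, and silence could not be taken as absence of events.

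The size is limited. Recording would allow a coarse description, with upper bounds of 31% for no events in an arm of 8 and 12% for none in the 24 snack participants, assuming full ascertainment and no dropout. The conclusion assumes that the V4 questionnaire and the interviews contain no structured question on side effects. None is described, and the stated rule suggests none is intended. The primary outcome, sample size and significance level are unaffected.

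**What to change.** Replace the sentence in Ethics and dissemination with: *Adverse events and digestive symptoms will be recorded daily by one item in the online food diary in all four arms and tabulated descriptively by arm.* Sensor-site or venepuncture-site problems can be noted through the same item, so no extra visit procedure is needed.

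The diary already runs throughout and is supervised daily. It therefore also covers the snack-free D7-D9 run-in, which gives some within-person background for digestive symptoms.

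The cost is a slightly longer diary entry, one descriptive table and a small amendment. The table should be presented as descriptive only. Because the trial is open-label, a common daily prompt evens out the opportunity to report but does not remove the effect of knowing one's snack.
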